## Abstract

**Background:**

Urgency is a complaint of sudden, compelling desire to pass urine, which is difficult to defer, caused by involuntary contraction of the detrusor muscle during the bladder-filling stage. To enable detrusor inhibition, electrotherapy resources such as transcutaneous tibial nerve stimulation (TTNS) and parasacral transcutaneous electrical stimulation (PTES) have been used. The objective this study is to publish the study protocol that aims to investigate whether urgency decreases after treatment with both of the techniques.

**Methods:**

This randomized controlled clinical trial will include 99 women, aged more than 18 years old, with urgency (score ≥ 8 in the Overactive Bladder-Validated 8-Question Awareness Tool [OAB-V8]). Women will be randomly allocated into three groups: TTNS, PTES, and placebo. The following questionnaires will be applied: the Anamnesis Record, the Incontinence Questionnaire Overactive Bladder, the King’s Health Questionnaire, the 24-Hour Voiding Diary, and the OAB-V8, at four different time points: at baseline prior to the first session, at the 6th session, the 12th session and at follow-up. The current used for the transcutaneous electrical stimulation will be a symmetrical balanced biphasic pulsed current, for 12 sessions, twice a week, for 20 minutes. Qualitative variables will be displayed as frequency and percentage, quantitative variables as mean and standard deviation. Comparison of urgency severity among groups will be performed with a repeated measures ANOVA, considering the effect of the three groups and the four evaluations, and interactions among them.

**Discussion:**

The present study aims to contribute evidence for a more in-depth discussion on electrode positioning for electrostimulation used in urgency treatment. It should be emphasized that, based on the possibility of confirming the hypothesis that urgency will decrease in a similar way after both treatments (TTNS and PTES), the PTES will be used as an option for positioning the electrodes alternatively to the tibial nerve region in special populations, such as amputees or people with severe lower limb sensory impairment.

**Trial registration:**

Brazilian Registry of Clinical Trials (ReBEC) ID: RBR-9rf33n, date of registration: 17 May 2018.

## Introduction

The International Continence Society defines urinary incontinence (UI) as any involuntary loss of urine [1, 2] and is classified as urinary stress incontinence, urgency urinary incontinence (UUI), and mixed urinary incontinence [3]. UUI occurs due to a contraction of the detrusor muscle at the bladder filling stage, with urine loss, accompanied or preceded by urgency [4]. An overactive bladder (OAB) occurs when there are symptoms of urgency with or without UI, usually polyuria and nocturia [4, 5].

UI is a public health problem, affecting, above all, older people [6] and women [7]. With regard to UUI, it is associated with a significant and clinically important decrease in health-related quality of life (QoL) [8, 9]. The prevalence of UUI is 1.8–30.5% in European populations, 1.7–36.4% in the United States, and 1.5–15.2% in Asian populations [10].

Electrical stimulation is used as a resource for UUI treatment in the physiotherapist’s clinical practice [11, 12]. Transcutaneous tibial nerve stimulation (TTNS) aims to facilitate inhibition of the detrusor muscle [13] by means of electrostimulation in the path of the tibial nerve [14]. The tibial nerve is a mixed nerve [15], that originates in the L5-S3 nerve roots, which are the same roots that innervate the parasympathetic pathway of the bladder (S2-S4) [14, 16], thus, it is suggested that direct stimulation of the tibial nerve could inhibit the S2-S3 afferents, thereby decreasing detrusor hyperactivity. This is a simple, non-invasive, well-tolerated technique considered conservative and effective therapy for patients with UUI [17] and OAB [11].

Guidelines, such as the Canadian Urological Association Guideline on Adult Overactive Bladder (2017) [5], European Association of Urology Guideline in Urinary Incontinence in Adults (2018) [13], and the American Urological Association/Society of Urodynamics, Female Pelvic Medicine and Urogenital Reconstruction Guideline: Overactive Bladder in Adults (2019) [18] report TTNS as the third line of treatment for UUI, with level of evidence B [5, 13] and C [18]. A recent systematic review noted the lack of protocol standardization for this technique, such as parameters, number of sessions, and duration of treatment [19]. There is a need for further research to confirm the efficacy of specific subgroups of patients as well as the magnitude of effect sizes associated with the ideal stimulation program and duration of effect [19]. On the other hand, a prospective cohort study found significant symptomatic improvement in all clinical parameters after treatment with TTNS in volunteers with UUI, with no adverse effects during treatment [17]. However, there are still gaps in the literature, and therefore studies with more consistent methods are needed, which strengthens the development of this study protocol using TTNS.

Another electrotherapy technique used in clinical practice is parasacral transcutaneous electrical stimulation (PTES), which uses a low-frequency current through transcutaneous electrodes in the sacral region (S3), with the aim of promoting an inhibitory reflex for detrusor muscle inhibition [20], and a consequent reduction in urgency. PTES is used in the treatment of voiding disorders in children [21–23] and clinical trials have reported positive effects for OAB in children and adolescents [24–26]. Sharma et al. [27] found a reduction in nocturia, urgency, and urge-incontinence in women with OAB, treated with PTES. However, the literature lacks more robust clinical trials using this form of application in adult women as well as clinical trials comparing the efficacy of PTES and TTNS.

The general objective of the research is to investigate whether urgency will decrease after treatment with transcutaneous electrostimulation in the tibial nerve or in the parasacral region. The hypothesis of the study is that urgency will decrease similarly after both treatments. The purpose of this article is to describe the methods and statistical analysis of this study, so that this information can be made public.

## Methods

### Trial design

This is a blinded randomized controlled trial. Outcome measures will be assessed at baseline (prior to initiation of treatment), during treatment (at the 6th session), on the last day of treatment (the 12th session), and 1 month after the completion of treatment (follow-up). Starting on March 1, 2017, participants were enrolled and randomized into three groups (TTNS, PTES, and placebo electrostimulation) by simple randomization using a 1: 1: 1 ratio. Data for the primary analysis will be collected by December 2019 and follow-up data by February 2020. Currently, no data analysis has been performed and the allocation of the groups remains blinded to the evaluator and the participants. The planning of this project followed the guidelines of the Consolidated Standards of Reporting Trials (CONSORT) and Standard Protocol items: recommendations for interventional trials (SPIRIT) guidelines.

### Ethics

The research was approved by the Ethics and Research Committee of the Federal University of São Carlos (CAAE: 79893917.1.0000.5504). Each participant will receive clarification regarding the research objectives, anonymity of their data, and freedom to participate. Participants will sign two copies of the Informed Consent Term (ICT). This study will respect the ethical precepts of Resolution CNS 510/2016 and be performed according to the Declaration of Helsinki. This study was registered in the Brazilian Registry of Clinical Trials (ReBEC) under number http://www.ensaiosclinicos.gov.br/ ID: RBR-9rf33n, http://www.ensaiosclinicos.gov.br/rg/RBR-9rf33n/, date of registration: May 17, 2018.

### Participants and settings

The trial is underway in the Laboratory of Research in Women’s Health (LAMU), in the Physiotherapy Department of the Federal University of São Carlos (UFSCar), in São Carlos, Brazil. Participants are being invited through informal invitation in social groups, and the research will also be disseminated through the internet on the UFSCar dissemination site and on social networks and leaflets. The objectives of the study will be explained by the researcher, who will clarify all doubts and questions in relation to the research, and individuals who agree to participate will sign the ICT. After selection of the participants, scheduling will take place for evaluations of eligibility of the sample and, later, for the start of treatment.

The inclusion criteria considered will be: women over 18 years of age; with urgency, self-reported and confirmed by a score greater than or equal to 8 on the Overactive Bladder – Validated 8-Question Awareness Tool (OAB-V8) [28] questionnaire. The exclusion criteria will be: stress urinary incontinence with no urgency symptom; urinary infection; alcoholism, smoking, or drug addiction; lesions and alteration in cutaneous sensitivity in the place where the electrotherapy will be applied; cognitive deficits; drug and/or physiotherapeutic treatment for UUI or current OAB; having any neurological disease; being in the gestational or puerperium period.

The presence of any signs of skin irritation that may be associated with electrostimulation will be considered as the criterion to discontinue the treatment. No concomitant care and interventions will be encouraged or prohibited during the study.

### Sample size

The calculation of the sample size was performed in G*Power 3.1.9.2 software, considering the comparison of three independent groups (TTNS, PTES, and placebo electrostimulation) in four distinct stages (pretreatment, 6th and 12th evaluation, follow-up), an analysis of variance (ANOVA) for repeated measurements, effect size of 0.15, significance level of 5%, and 90% test power, resulting in a total of 99 participants in the study (33 participants per group).

### Randomization and allocation

Once included, initial evaluations will be conducted before participants are randomized (1: 1:1) to three groups (TTNS, PTES, and placebo electrostimulation, Fig. 1), using simple randomization, conducted by an investigator who is not involved with the recruitment and treatment of participants.

**Fig. 1 Fig1:**
[figure not shown]
Trial flow diagram. *24 h-VD* 24-Hour Voiding Diary;; *ICQ-OAB* Incontinence Questionnaire Overactive Bladder; *KHQ* King’s Health Questionnaire; *OAB-V8* Overactive Bladder – Validated 8-Question Awareness Tool

Ninety-nine pieces of paper cut in rectangular form in three distinct colors, corresponding to TTNS, PTES, and placebo, respectively, will be placed inside a brown envelope. The volunteer will remove 1 (one) piece of colored paper from the envelope and then show it to the blind evaluator, who will record the color of the treatment drawn.

On the first day of treatment the physiotherapist will check the color chosen and apply the corresponding technique. This physiotherapist will not be involved in the randomization, evaluations, or re-evaluations of the participants. Participants will be informed that they will receive one of three different forms of application of electrostimulation, but will be blinded to the hypothesis of the study.

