### Evaluation tools

After the participants sign the ICT, an investigator will apply validated questionnaires that measure the severity of the OAB (Overactive Bladder – Validated 8- Question Awareness Tool; OAB-V8) and UUI (Incontinence Questionnaire Overactive Bladder; ICIQ-OAB), and quality of life, specifically the history of urgency and urinary incontinence (King’s Health Questionnaire; KHQ). The participant will be given a 24 hour Voiding Diary (24 h-VD) (the participant will be asked to deliver the completed diary on the first day of treatment). In the 6th and 12th sessions, these four questionnaires will again be completed as a way of evaluating the course of treatment, by the same evaluator blind in relation to the groups (Table 1).

**Table 1 Tab1:** Data collection/measurement of results

	Pretreatment	1st Session	2nd Session	3rd Session	4th Session	5th Session	6th Session	7th Session	8th Session	9th Session	10th Session	12th Session	Follow-Up
Anamnesis record	+												
OAB-V8	+						+					+	+
ICIQ-OAB	+						+					+	+
KHQ	+						+					+	
24 h-VD	+						+					+	
Session Monitoring Card		+	+	+	+	+	+	+	+	+	+	+	
Follow-up Monitoring Card													*+*

*24 h-VD* 24-Hour Voiding Diary; *ICIQ-OAB* Incontinence Questionnaire Overactive Bladder; *KHQ* King’s Health Questionnaire; *OAB-V8* Overactive Bladder – Validated 8-Question Awareness Tool

The OAB-V8 is an instrument translated and validated for Portuguese [28]. It includes eight questions alluding to an initial general statement “How much have you been bothered by ...”. As options for answers, there are six variations “Never; Almost nothing; A little; Enough; A lot, and Very Much”. The score of this instrument is calculated through the sum of the questions, and can vary from 0 to 40 points; if the result is 8 or more than 8, it is indicative of OAB [28]. The ICIQ-OAB has been translated, adapted, and validated into Portuguese [29]. This is a short questionnaire with a high psychometric capacity to evaluate OAB, capable of assessing the impact of symptoms of urinary frequency, urgency, nocturia, and incontinence [30]. It consists of four basic questions: question 3a investigates urinary frequency, question 4a evaluates nocturia, and questions 5a and 6a investigate urgency and UUI, respectively. For the analysis of the results, the corresponding values of questions 3a, 4a, 5a, and 6a are added, obtaining a total of 0 to 16 points; the higher the value found, the greater the impairment [29].

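### The evaluator meant to stay blind records each woman's allocation colour, so one unambiguous disclosure would decode a whole arm; the draw is also not simple randomization

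*Protocol article*

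**What the plan says.** The text below Figure 1, under Randomization and allocation, describes "Ninety-nine pieces of paper cut in rectangular form in three distinct colors, corresponding to TTNS, PTES, and placebo, respectively", placed in one envelope. The woman draws one slip and must "show it to the blind evaluator, who will record the color of the treatment drawn". The colour leads straight to the treatment: "On the first day of treatment the physiotherapist will check the color chosen and apply the corresponding technique". That therapist is kept apart from the rest of the process: "This physiotherapist will not be involved in the randomization, evaluations, or re-evaluations of the participants". The article makes no such statement about the evaluator.

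The same section says that allocation is made "using simple randomization, conducted by an investigator who is not involved with the recruitment and treatment of participants". Outcome assessment is not among the roles from which this investigator is excluded.

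Under Evaluation tools, the four instruments given at baseline are completed again at sessions 6 and 12 "by the same evaluator blind in relation to the groups". For the one-month follow-up, the article speaks only of a blinded investigator. Under Minimizing missing data, the blinded evaluator telephones each woman about three days before that visit. The section on outcomes makes urgency by OAB-V8 the primary outcome and adds urgency episodes from the monitoring cards, also as primary.

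Trial design and Randomization and allocation both call the method simple randomization.

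**The concern.** The person who must not know the allocation holds a participant-level list of it, in a code with three entries that is the same for every woman. The only protection is that this person does not know what the three colours mean. The evaluator has repeated contact with women who feel where they are stimulated, and the Discussion concedes that participants cannot be blinded to the therapy. If one of them makes her arm plain, the list gives the arm of every other woman with her colour.

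Evaluator blinding carries weight here. The treating physiotherapist cannot be blinded, and the article is not consistent on participants: the Blinding section says that they cannot be blinded to the stimulation but are blinded to their group. If the evaluator learned the key, knowledge of the arm could affect how the questionnaires are introduced, prompted and clarified after baseline.

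The label is a smaller matter. A reader who is told that simple randomization was used would picture independent assignments with free arm sizes. The described draw is something else.

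**Working it through.** **1. Arm size.** Sample size gives 99 in total, 33 per group, from a repeated-measures ANOVA with 3 groups, 4 occasions, effect size f = 0.15, alpha 5% and power 90%. With a within-between interaction, correlation 0.5 and sphericity (all three assumed, since the article does not state them), lambda = f² × N × m / (1 − rho) = 0.0225 × 99 × 4 / 0.5 = 17.82, with df = 2 × 3 = 6 and 96 × 3 = 288. Power is 0.900 at N = 99 and 0.889 at N = 96, so the stated figure reproduces. With three colours, 99 / 3 = 33 women share each colour.

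**2. Which remarks decode a colour.** From Interventions:

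| Arm | Electrode sites | Site with current |
|---|---|---|
| TTNS | tibial | tibial |
| PTES | parasacral | parasacral |
| Placebo | tibial, parasacral, scapular | scapular only |

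A remark about electrodes at the ankle fits TTNS and placebo. A remark about electrodes at the sacrum fits PTES and placebo. Either one narrows a colour to two arms but does not settle it. A remark is unambiguous if it tells where current was felt, mentions the scapula, or tells one site from three.

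**3. Exposure per unambiguous disclosure.**
- One arm disclosed: up to 33 of 99 women (33%).
- Two arms disclosed: all 99, because the third colour follows by elimination.
- With participant-specific codes: one woman per disclosure.

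**4. Illustration.** Let p be the chance that a woman makes an unambiguous disclosure to the evaluator, independently of the others. The documents give no value, so a range is shown. For one arm, q = 1 − (1 − p)^33. At least one arm is decoded with probability 1 − (1 − q)³, and all three with probability 3q²(1 − q) + q³. With separate codes, the expected number unblinded is 99p.

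| p | At least one arm decoded | All arms decoded | Women unblinded with separate codes |
|---|---|---|---|
| 1% | 63% | 19% | about 1 |
| 2% | 86% | 48% | about 2 |
| 5% | 99% | 91% | about 5 |
| 10% | >99.9% | >99% | about 10 |

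These figures cover the whole trial and show how a shared code multiplies a rare event. They do not estimate what happened.

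**5. Randomization label.** The fixed total of 99 slips and 33 per group imply 33 slips per colour, drawn without replacement (inferred). Final arm sizes are then certain. Under simple randomization, the chance of exactly 33/33/33 is 99! / (33!)³ / 3^99, about 0.8%.

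**6. Predictability of the draw.** Someone with the full log who always names the commonest remaining colour is right about 40 times in 99, against 33 by chance (20,000 simulated draws). The rate is about 36% over the first 52 draws, 52% over the last 20 and 60% over the last 10. The last draw is certain. What is predicted is a colour, not an arm.

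**The case against.** A colour whose key the evaluator does not hold is coded allocation, and the article calls the evaluator blind in several places. No leak is reported, and how the key is held is operational detail that an article may leave to the full protocol. This stands in part: blinding is intact until the key leaks. But the recording of colours by the evaluator is a stated procedure, not a missing detail. A woman who talks unblinds herself under any scheme; the avoidable harm is to the others who share her colour.

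The recorder of the slip and the outcome assessor may be different people. Their identity is inferred from the shared label, and the follow-up assessor is named only as a blinded investigator. If the roles are separate, the text should say so.

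The OAB-V8 is the sum of the woman's own answers on fixed options, so the evaluator does not rate severity. This stands and limits the possible bias to how the questionnaire is applied. Urgency episodes come from monitoring cards; the session cards are described as completed by the participant, so they do not clearly pass through the evaluator.

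Two stronger readings are tempting. A reader might infer that any mention of the ankle or the sacrum decodes a colour. The three-site placebo placement rules that out. A reader might also infer from the late-draw figures that allocation concealment fails and selection bias follows. That would need both a leaked key and a log-holder able to influence who enrols or when. The article shows neither: allocation follows inclusion and baseline evaluation, and the woman draws her own slip.

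**Conclusion.** The concern holds as a conditional weakness in how the allocation is coded and recorded. The stated procedure gives the evaluator a participant-level list protected only by ignorance of a three-colour key. One unambiguous disclosure exposes up to 33 women and disclosures from two arms expose all 99, against one woman per disclosure with separate codes. The documents do not show that blinding has failed, and the effect on the OAB-V8 would be indirect.

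This rests on two inferences: that the evaluator who records the slip is the one who assesses at sessions 6 and 12, and that each colour has 33 slips. The probabilities in the illustration rest on an assumed disclosure risk.

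Separately, the method is mislabelled: it is a restricted draw of 33 per arm. The predictability of late colours is secondary and is not evidence of selection bias.

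**What to change.** Trial status reports 52 women who have completed follow-up, so at most 99 − 52 = 47 allocations remain. For these:

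- The evaluator neither sees nor records the colour. The woman seals her slip in an opaque envelope marked with her study number, and the treating physiotherapist opens it at the first session.
- Someone with no role in outcome assessment keeps the log. The investigator who conducts the randomization can do this only if confirmed not to be an evaluator, since the article excludes that person from recruitment and treatment alone.
- The existing log leaves the evaluator's hands now.
- The colour-to-arm key is reassigned for undrawn slips, so that colours already seen do not carry over. The number left per arm must be kept, for instance by replacing the slips with unused colours; permuting the present three would upset 33 per arm if unequal numbers remain. Women already allocated stay under the old key.
- The article and the trial report describe a restricted draw of 33 per arm, and the report states that the evaluator saw colour codes for the earlier participants.

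The cost is a small change of procedure, envelopes, and two keys in use for a time. If the randomizing investigator does turn out to be an evaluator, another person must keep the log. The sample size does not change. The fix does not protect allocations already recorded, because moving the log cannot erase what the evaluator has seen.

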### Evaluation tools

After the participants sign the ICT, an investigator will apply validated questionnaires that measure the severity of the OAB (Overactive Bladder – Validated 8- Question Awareness Tool; OAB-V8) and UUI (Incontinence Questionnaire Overactive Bladder; ICIQ-OAB), and quality of life, specifically the history of urgency and urinary incontinence (King’s Health Questionnaire; KHQ). The participant will be given a 24 hour Voiding Diary (24 h-VD) (the participant will be asked to deliver the completed diary on the first day of treatment). In the 6th and 12th sessions, these four questionnaires will again be completed as a way of evaluating the course of treatment, by the same evaluator blind in relation to the groups (Table 1).

**Table 1 Tab1:** Data collection/measurement of results

	Pretreatment	1st Session	2nd Session	3rd Session	4th Session	5th Session	6th Session	7th Session	8th Session	9th Session	10th Session	12th Session	Follow-Up
Anamnesis record	+												
OAB-V8	+						+					+	+
ICIQ-OAB	+						+					+	+
KHQ	+						+					+	
24 h-VD	+						+					+	
Session Monitoring Card		+	+	+	+	+	+	+	+	+	+	+	
Follow-up Monitoring Card													*+*

*24 h-VD* 24-Hour Voiding Diary; *ICIQ-OAB* Incontinence Questionnaire Overactive Bladder; *KHQ* King’s Health Questionnaire; *OAB-V8* Overactive Bladder – Validated 8-Question Awareness Tool

The OAB-V8 is an instrument translated and validated for Portuguese [28]. It includes eight questions alluding to an initial general statement “How much have you been bothered by ...”. As options for answers, there are six variations “Never; Almost nothing; A little; Enough; A lot, and Very Much”. The score of this instrument is calculated through the sum of the questions, and can vary from 0 to 40 points; if the result is 8 or more than 8, it is indicative of OAB [28]. The ICIQ-OAB has been translated, adapted, and validated into Portuguese [29]. This is a short questionnaire with a high psychometric capacity to evaluate OAB, capable of assessing the impact of symptoms of urinary frequency, urgency, nocturia, and incontinence [30]. It consists of four basic questions: question 3a investigates urinary frequency, question 4a evaluates nocturia, and questions 5a and 6a investigate urgency and UUI, respectively. For the analysis of the results, the corresponding values of questions 3a, 4a, 5a, and 6a are added, obtaining a total of 0 to 16 points; the higher the value found, the greater the impairment [29].

The KHQ has been translated and validated into the Portuguese language [31]. This questionnaire is specific to UI [32]. The KHQ consists of 30 questions, divided into eight domains: general health perception, impact of UI, limitations of daily activities, physical limitations, social limitations, personal relationships, emotions, sleep/mood. The questionnaire also contains two other independent scales: one assesses the severity of UI (severity measures) and the other the presence and intensity of urinary symptoms (urinary symptom scale). The KHQ is scored in domains, so there is no overall score. The scores range from 0 to 100 and the higher the score obtained, the worse the quality of life related to that domain [31].

The 24 h-VD [3], contains data on urinary habits, and should be completed for a period of 24 hours, with information on number of urinations; amount of urine eliminated; and occurrence of urinary loss or urgency. During the study, the participant will complete the diary 3 times, referring to pretreatment, middle of treatment (6th session), and end of treatment (12th session).

During the treatment, in order to follow the micturition symptoms per session, a Session Monitoring Card will be used. This fact sheet contains open and closed questions about the urinary symptoms of the day before the session and the day of the session. It also contains a Visual Analogue Scale (VAS) [33] to indicate possible discomfort of the applied technique. The volunteer will be questioned as to their degree of discomfort during the treatment, with 0 indicating total absence and 10 the maximum level of discomfort bearable. Any side effects that the participants report will be recorded by the researcher. Over the 12 sessions, each participant will complete 12 Session Monitoring Cards, thus allowing longitudinal analysis of the voiding symptoms.

One month after completion of treatment, an investigator, blinded to the allocation of participants, will complete a Follow-up Monitoring Card. In addition to this card, the ICIQ-OAB and OAB-V8 will also be applied.

